**Fig. 1 Fig1:**
[figure not shown]
Standard Protocol Items: Recommendations for Interventional Trials (SPIRIT) Schedule of enrolment, intervention and assessments. T1 data collection: RA1 will collect demographic data and T1 outcome measures will be administered individually by telephone. Participants will be informed that they will be notified about the start date of their group. T2 and T3 post intervention data collection: At the end of the first intervention, all participants will be contacted by telephone to conduct individual T2 assessments. For T3 data collection, all participants will be contacted by telephone by RA1 to conduct individual assessments

### Sample size justification

A sample size of 48 participants will allow for intervention group sizes of six participants and wait listed control group sizes of six participants. There will be four blocks of participants, with 12 participants in each block, and groups of six participants. This will result in 24 participants per arm. Small sample sizes of 10–20 participants or more are appropriate for pilot testing of adherence to interventions and this study will exceed those numbers, thereby allowing for attrition [48, 49]. There are also pragmatic considerations to selecting the sample size for this study [50], which include planning to complete the study within a year with limited funding. The study will not be powered to detect significant changes on the secondary outcomes. As COVID-19 protocols prohibit groups meeting in person, this study has moved to Zoom, an online privacy protected platform [51]. Other COVID-19 adjustments pivots required will be shorter meetings of 1.5 h to avoid Zoom fatigue and smaller group sizes [40]. This will be sufficient to meet the study’s primary objectives of recruitment, retention, and completion rates to determine whether a large study is warranted.

### Recruitment

Adults 55 years of age and older will be recruited through two primary care clinics in Eastern Ontario, Ontario-based community organizations that support older adults, and community referrals through traditional snowball effect [52]. The PI will screen potential participants for eligibility. The following participant characteristic data will be collected by the PI at the time of enrolment into the study: age, gender, working status, educational status, marital status, living situation, and how many times, if at all, the participant presently meditates per week. Referrals to the PI will be made by health care providers, staff at community-based organizations supporting older adults, and through community spread. Referees and self-referring community-based potential participants will be informed of the study through email, advertisements on a local radio station’s website, and social media. All costs associated with recruitment will be self-funded by the PI, a PhD candidate. Duration of recruitment will be monitored by the PI and her PhD advisors. No financial incentives will be offered to participants. Potential benefits to participants will be receipt of instruction in a mindfulness-based meditation therapy group. The possible benefit to society at will be to determine the feasibility of a scalable treatment for older adults with anxiety.

### Randomization

Random allocation will be conducted by the second author, immediately after each set of 12 participants has been enrolled into the study by the PI*.* Groups will begin on a rolling basis each time a block of 12 participants has been enrolled. To ensure a 1:1 random allocation between the intervention and control groups, the participants will be randomly assigned using the random allocation function in Excel.

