**Methods:**

This pilot feasibility randomized controlled trial will use a wait list control trial design. Due to COVID-19 restrictions, we will use telehealth delivery via Zoom rather than in-person delivery. The first 48 people to meet the eligibility criteria will be randomly allocated to either receive EFMT immediately, or in approximately 8 weeks time from enrollment (1:1 allocation ratio). Data will be collected at baseline, 8 weeks following baseline, and 16 weeks following baseline. The primary outcomes will determine the feasibility of the intervention based on recruitment, enrolment, retention, and adherence to all components of the intervention. The secondary outcome will be changes to anxiety over time.

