### Design and setting

The study is a feasibility randomized controlled trial (RCT) using a wait list control trial design. Due to COVID-19 restrictions, this study has been adapted from in-person delivery to telehealth delivery via Zoom. The first 48 people to meet the eligibility criteria will be randomly allocated to receive EFMT immediately, or in 8 weeks from time of baseline assessment (1:1 allocation ratio). Data will be collected by a blinded to group research assistant (RA) at baseline (T1), 8 weeks following baseline (T2), and 16 weeks following baseline (T3). Participants will be recruited from primary care clinics and community organizations that provide support to older adults. The principal investigator (PI)/facilitator of the EFMT groups will be blinded to the results of outcome assessments until the end of the intervention phase of the study. The PI is a registered psychotherapist certified in delivering EFMT and will facilitate all groups.

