### Interventions

#### Comparators

The comparator will be no treatment (treatment as usual) for the controlled wait list group. All participants will receive the intervention. All participants will receive T1, T2, and T3 assessments within 7–10 days of each timepoint.

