#### Collection of information at T2

All participants will be contacted by telephone by the RA to re-administer the GAI, PSQI, and MMSQ within 1 week of completion of the intervention.

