#### Collection of information at T3

All participants will be contacted by telephone by the RA to re-administer the GAI, PSQI, and MMSQ and to collect data on extraneous life events, within 1 week of completion of the intervention for the wait list control group. The RA will attempt to collect data from all participants whether or not all sessions are attended.

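### T2 and T3 have two conflicting anchors, weeks since baseline and completion of the groups, and nothing ties baseline to the date a group starts

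*Protocol article*

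**What the plan says.** **Calendar rule.** The protocol article, Design and setting, places the follow-up assessments at "8 weeks following baseline (T2), and 16 weeks following baseline (T3", counted from each person's own baseline.

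**Completion rule.** The Fig. 1 legend says "At the end of the first intervention, all participants will be contacted by telephone to conduct individual T2 assessments". Collection of information at T2 has the assessments repeated "within 1 week of completion of the intervention". Collection of information at T3 uses "within 1 week of completion of the intervention for the wait list control group".

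**Window.** Comparators adds: "All participants will receive T1, T2, and T3 assessments within 7–10 days of each timepoint". It does not say which of the two definitions the window surrounds.

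**Group start.** Under Randomization, allocation takes place "immediately after each set of 12 participants has been enrolled into the study by the PI", and "Groups will begin on a rolling basis each time a block of 12 participants has been enrolled".

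**Wait-list start.** Design and setting counts the 8-week wait from the baseline assessment. The Methods part of the abstract has the second group start "in approximately 8 weeks time from enrollment".

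**Date of T1.** No section says whether T1 is done as each person enrols or once the block is full. The Fig. 1 legend implies only that T1 comes before participants learn their start date.

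**The concern.** A block of 12 takes time to fill, and nobody in it starts until it is full. If baselines are spread over that period, the two rules give different T2 and T3 dates for the same person. Six people with different baseline dates who share one group also cannot each start exactly 8 weeks after their own baseline.

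What is at stake depends on which rule the assessor follows:

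- Under the calendar rule, some immediate-arm participants would be assessed at T2 before their programme ends. T2 is the only follow-up at which one arm has been offered the programme and the other has not.
- Under the completion rule, the interval from T1 to T2 varies from person to person and includes weeks before treatment began. Those weeks enter the within-person change that Statistical methods analyses with a pooled paired t-test and, in the intervention group, a repeated-measures ANOVA over T1, T2 and T3.

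The Discussion says the findings will inform sample size calculations for a definitive trial, so the meaning of these change scores matters even though the pilot is not powered on them.

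**Working it through.** **Inputs from the protocol article**

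- 48 enrolled in 3 months, given as 16 per month (Outcome collection and measures).
- Four blocks of 12, in groups of six (Sample size justification).
- Eight weekly meetings (Intervention description), so session 8 falls 7 × 7 = 49 days after session 1.
- T2 at 8 weeks = day 56, with a window of 7 to 10 days (Design and setting; Comparators).

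**The plan's own figures reproduce:** 48 / 3 = 16 per month; 4 × 12 = 48; 4 × 6 = 24 per arm.

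**Assumptions, not in the document:** T1 on the day of enrolment; evenly spaced enrolment; a month of 30.44 days; session 1 on the day the 12th person enrols, unless stated otherwise.

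**Waiting time**

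- Spacing = 30.44 / 16 = 1.90 days.
- Wait of the i-th person in a block = (12 − i) × 1.90 days.
- Longest wait = 11 × 1.90 = 20.9 days; mean wait = 10.5 days.

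**Calendar rule.** T2 precedes session 8 when wait + 49 exceeds the T2 day. That means a wait over 7 days for day 56, over 14 for day 63 and over 17 for day 66. Allocation is 1:1 within the block, so the share of the block applied to 24 gives the expected number in the immediate arm.

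| Scenario | T2 at day 56 | T2 at day 63 | T2 at day 66 |
|---|---|---|---|
| 16 per month, immediate start | 8 of 12 (16 of 24) | 4 of 12 (8 of 24) | 3 of 12 (6 of 24) |
| 16 per month, session 1 a week after the block fills | 11 of 12 (22 of 24) | 8 of 12 (16 of 24) | 6 of 12 (12 of 24) |
| 8 per month, immediate start | 10 of 12 (20 of 24) | 8 of 12 (16 of 24) | 7 of 12 (14 of 24) |

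With random (Poisson) arrivals at 16 per month and an immediate start, simulation gives 61%, 32% and 21%, close to the first row.

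In the first row, sessions held by day 56 = floor((56 − wait) / 7) + 1. For the first enrollee this is floor(35.1 / 7) + 1 = 6.

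**Completion rule.** No T2 precedes session 8. For the first enrollee, session 8 falls at 20.9 + 49 = 69.9 days and the one-week limit runs to 76.9 days, which is 10 to 11 weeks after baseline instead of 8.

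**Can both rules be met?** For the first three enrollees in a block, session 8 falls at about days 69.9, 68.0 and 66.1. All three are past day 66, the latest edge of the calendar window, so under these assumptions no T2 date satisfies both rules for an immediate-arm participant in those positions.

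**If T1 is taken once the block is full.** With T1 no more than 7 days before session 1, session 8 falls by day 7 + 49 = 56. The two rules then agree within the window, and essentially no T2 is early.

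**The case against.** The strongest reply is that the sections describing how assessments are actually made all tie T2 and T3 to completion, and that 8 and 16 weeks are nominal labels for an eight-session programme. The abstract's own wait-list wording is approximate. T1 is a separate telephone call by the research assistant, so it may well be made once the block is full. A condensed article may also leave call scheduling to the full protocol.

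Much of this stands. A reader might infer that many T2 assessments will fall before the last sessions. The document does not support that as a flat statement: it needs both T1 at individual enrolment, which is not stated, and the calendar rule being the one followed. A reader might also apply 8 of 12 to all participants. Wait-list members have T2 before treatment by design, so only the 24 in the immediate arm can be assessed mid-programme at T2.

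A further inference would be that pre-treatment drift biases the comparison of arms. It does not: allocation follows block filling, so waiting time is balanced between arms in expectation. The between-arm t-test that Statistical methods names is in any case placed at T3.

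Dilution at T2 should not be overstated either. At the planned rate even the earliest enrollee has reached session 6 by day 56, and attending six of eight sessions counts as completing the intervention under Feasibility and acceptability outcomes.

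The reply does not remove the contradiction. The article states two rules for the same visits, does not mark either as nominal, and gives no date for T1 that would make them agree. That is a conflict in what is written, not a detail left out.

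**Conclusion.** The conflict between the two anchors is on the page and needs no assumption; so is the split between baseline and enrolment for the wait-list start. Its size is conditional. With T1 at enrolment and the planned 16 per month, about 16 of 24 immediate-arm T2 assessments precede session 8 at exactly day 56, falling to about 6 of 24 with the window used 10 days late. Slower enrolment or a delayed first session raises these figures. Under the completion rule the count is zero, and the cost is a T1-to-T2 interval of up to 10 to 11 weeks that mixes untreated time into the within-person analyses. If T1 is taken when the block is full, the problem essentially disappears.

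The outcomes concerned are secondary, and the trial is not powered for them. The primary criteria on consent, recruitment pace, retention, attendance and component adherence do not depend on this interval. It should be corrected, but it does not threaten the trial's main purpose.

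**What to change.** Use one anchor throughout:

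- Take T1 for all 12 members of a block in a short window after the block fills and before allocation is released.
- Tie T2 to the end of the first group and T3 to the end of the wait-list group, with the same calendar window for both arms of the block.
- Mark 8 and 16 weeks as nominal, and count the wait-list start from the same block-level date in the abstract and in Design and setting.
- Record the actual days since T1 and the sessions completed at T2, so that the analysis can describe any remaining variation.

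The cost is a wording change, 12 T1 calls made in a batch for each block, and a few days' delay between a block filling and release of its allocation.

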### Blinding

RA will be blinded to participant allocation to ensure unbiased assessment administration and data collection throughout the study. Participants will be masked from the group to which they have been allocated. The PI will remain concealed to the outcome measurements data until all participants have completed the intervention and statistical analysis has begun. Unblinding and unmasking may unintentionally occur. It is possible that the RA may be unblinded to the allocation of participants who may unintentionally reveal their assignment to group during the collection of T2 outcome measures. This is a pragmatic reality of conducting a small scale self-funded PhD-based study.

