### Participant retention

The PI will encourage participant retention by sending reminder emails of group start dates to wait listed participants at 4 weeks, 2 weeks, and 1 week prior to the beginning of the group.

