### Data management

All data forms will be uploaded to the Microsoft Teams environment, password protected, and backed up in the Queen’s University cloud storage. The RA will enter all data in SPSS [68]. Data will be kept for seven to 10 years after. Data will be held in a secure environment on Canadian servers in the Queen’s University research data repository for faculty, students, and staff [65].

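### The plan says participants are masked to allocation, which a wait list design cannot achieve once groups start, and it sets no limit on session records reaching the blinded assessor through data entry

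*Protocol article*

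**What the plan says.** Three statements in the Blinding section of the protocol article matter here.

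- Participants: "Participants will be masked from the group to which they have been allocated".
- Assessor: "RA will be blinded to participant allocation to ensure unbiased assessment administration and data collection throughout the study".
- Caveat: "Unblinding and unmasking may unintentionally occur". One route is then described: "It is possible that the RA may be unblinded to the allocation of participants who may unintentionally reveal their assignment to group", at the T2 call.

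Other sections describe what participants experience. Design and setting has EFMT starting immediately or 8 weeks after baseline. Under Comparators: "The comparator will be no treatment (treatment as usual) for the controlled wait list group". Participant retention plans on "sending reminder emails of group start dates to wait listed participants", at 4, 2 and 1 weeks before their group begins. The Fig. 1 legend says of the T1 call: "Participants will be informed that they will be notified about the start date of their group". It places T2 at the end of the first intervention period.

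On data handling, Data management says: "The RA will enter all data in SPSS". Statistical methods also assigns data entry to the RA. Neither section says when entry takes place or which records the RA may see before the assessments are finished.

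**The concern.** In a wait list trial the allocation is the start date. A participant cannot attend eight weekly group sessions, or wait eight weeks for them, without knowing which of the two is happening. An unqualified claim of participant masking therefore describes a property the design does not have.

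The secondary outcomes are what is at stake. The Geriatric Anxiety Inventory (GAI), Pittsburgh Sleep Quality Index (PSQI) and Multifactorial Memory Questionnaire (MMQ) are scored from what participants say. People who know they have had the therapy may report improvement, and people who know they are waiting may report none. Statistical methods plans Cohen's d for these outcomes, and the Discussion says the findings will inform sample size calculations for a definitive trial. An effect size read as coming from masked participants could be given more weight in that planning than it deserves.

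The second issue concerns the one person whose blinding is feasible. The RA is to stay blind throughout and is also to enter all the data, while the trial generates records whose mere existence identifies the arm.

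**Working it through.** No formula applies, and the plan gives no figure to reproduce. The check sets the sections side by side.

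**Participant masking, by timepoint**

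1. *T1 (baseline).* The Fig. 1 legend has participants told only that a start date will follow. Under Randomization, allocation happens after each set of 12 has been enrolled. Masking at T1 is plausible.
2. *Between T1 and T2.* The immediate arm begins sessions. Reminders go to the wait-listed arm 4, 2 and 1 weeks before its group starts. If that group starts at week 8 after baseline, as Design and setting states, the reminders fall at weeks 8 − 4 = 4, 8 − 2 = 6 and 8 − 1 = 7, all before T2 at week 8.
3. *T2 (8 weeks).* One arm has been offered the full programme and the other none of it. Each participant knows which applies. With 24 per arm, 24 + 24 = 48 of 48 are unmasked by design.
4. *T3 (16 weeks).* Both arms have been offered EFMT, and participants still know which start they were given.

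**Which analyses this touches**

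- The stated secondary objectives compare people who receive EFMT with people who do not. Only T2 offers that contrast.
- Statistical methods places the between-group t-test at T3. It also plans a pooled paired t-test against baseline and a repeated measures ANOVA in the intervention group. Every one of these uses answers given after allocation by participants who know their treatment status.
- The T1 data collection section calls the PSQI subjective and the MMQ self-report. The GAI is read out by the RA, but its answers also come from the participant.
- The criteria for recruitment (70% of eligible people consenting, 48 enrolled in 3 months) and retention (65%) are counts. They do not rest on masking.

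**RA blinding and data entry**

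1. Blinding requires the RA to be blind for the whole study.
2. Data management and Statistical methods give the RA all data entry.
3. Outcome collection and measures shows that the data include attendance, observed meditation, journaling and reporting, and weekly forms on home practice.
4. In the first 8 weeks of a block, attendance and in-session adherence records can exist only for the immediate arm. A study identifier in place of a name does not hide this, because the RA needs the same identifier to file the T1 to T3 scores.
5. Groups start on a rolling basis, block by block, so session records from early blocks exist while later assessments are still due.
6. Statistical methods ties analysis to the end of the study but does not tie entry to it.

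Steps 1 to 5 show a route by which the blind could be lost. Step 6 shows that the document does not close it. Whether the route would be used depends on the timing of entry, which is not given.

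**The case against.** The strongest defence has four parts.

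*The plan admits that masking may fail.* The Blinding section says so in general terms, and in context this covers participants as well as the RA. That must be acknowledged. But the wording treats as an accidental possibility something that is certain for participants, so it does not repair the claim.

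*The data-entry problem is not shown to occur.* This largely stands. The weekly forms go to the principal investigator (PI), who also documents adherence, and data carry only a study identifier. Entering session records after the last T3 would fit every sentence in the article. A reader might infer that the RA will be unblinded before T2, or that all 48 allocations will be visible to the RA. The document supports neither, because it does not say when entry happens. A condensed article may also leave access rules to the full protocol. What remains is that two rules stated in the article pull against each other unless a restriction is added.

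*RA blinding still has value.* This stands. Its stated purpose is unbiased administration and data collection, and it can limit bias in how three telephone scales are asked and scored. A reader might infer that the outcomes have no protection at all. That goes too far, because baseline is collected before start dates are notified and the interviewer can remain blind.

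*Only unpowered secondary outcomes are affected.* This is correct. Sample size justification says the study is not powered for them, and the Discussion disclaims hypothesis testing. It limits the importance of the point. It does not make an incorrect masking statement harmless when effect sizes will be reported and used for planning.

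**Conclusion.** The point holds in two parts of different strength.

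The participant-masking statement is wrong for every assessment after allocation. Unmasking is 48 of 48 by design if the target is met, and this rests on nothing beyond the wait list structure. Post-allocation GAI, PSQI and MMQ results, and any Cohen's d from them, are open to expectation bias that a blinded interviewer cannot remove. Its direction and size in SD units cannot be derived from the document.

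The RA's blinding is left unguarded, which is a conditional weakness and not a demonstrated failure. It rests on one assumption: that attendance, adherence or weekly home-practice records reach the RA before the assessments are complete. If they do not, data entry does no harm.

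The recruitment, enrolment and retention criteria are unaffected. The correction is worth making because it is nearly free and because the secondary estimates are meant to inform a larger trial.

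**What to change.** 1. In Blinding, delete the statement that participants are masked. State instead that participants and the facilitator are unblinded after allocation, that the secondary outcomes rest on participants' own answers, and that only the RA interviewer is intended to be blind. The provision keeping the PI from the outcome data can stay.
2. In Data management, state that attendance, adherence and weekly home-practice records are withheld from the RA until the last T3 assessment, and that the RA enters them after that point. Until then the PI, who already receives or produces them, keeps them where the RA has no access. This also avoids having the facilitator who judges adherence enter those data.
3. Where the secondary effect sizes are reported, note that they come from unmasked participants.

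An RA guess of allocation at the end of each T2 call would be an optional extra and is not needed to correct the plan.

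The cost is a change of wording, a less favourable statement about bias, and later entry and error-checking of session data. Analysis is already planned for the end of the study, so no planned analysis needs the earlier entry. Sample size, intervention and assessment schedule do not change.
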